### Statistical Issues

#### Sample size, clinical significance, statistical significance

We want to ensure that our clinical trial has adequate statistical power to detect a clinically significant difference of at least 6 mmHg at 1 year in systolic BP between groups with a two-tailed significance level of 0.05. Assuming a standard deviation of 15 mmHg and a 20% loss to follow-up, we would need to randomize 110 participants per group. We expect a 15% "contamination" of the control group (see below), yielding a 1.41 contamination effect [26]. Thus, the final target sample size is 320 patients.

The effectiveness of the intervention will be assessed by a clinically significant reduction in BP, cardiovascular mortality models shows an estimated 5-yr risk reduction of cardiovascular disease of 15-20% by a reduction of 5 mmHg in systolic blood pressure [27,28]. We have estimated that a difference of at least 10 mmHg at 1-yr is necessary to detect a clinically significant difference of at least 5 mm Hg at 5-yr.

Intervention will be provided to a group of participants by a single nurse, so we will consider the cluster effect during statistical analysis.

#### Data collection and management

We will collect information on outcome at every stage of the recruitment, randomization, treatment allocation, follow-up, and analysis so that we can report patient flow according to CONSORT guidelines [29]. We will record the number of patients who qualified for inclusion but who were not willing to participate, the number of patients assigned to the intervention arm, the number of patients assigned to the control arm, the number of intervention visits, the number of patients who provide follow-up data, the number of patients who complete the trial and are included in the analysis, and the number of withdrawals.

We will implement procedures to ensure that randomization proceeds as planned, that clinical data collection forms are accurately entered into databases, and that data are accurately transferred and retrieved as needed. We will use a relational database to track information during recruitment, randomization, treatment, and assessment so that we can report patient flow automatically and in an integrated fashion by use of standard automated reports. To ensure accurate transfer of information, all data system processes will be thoroughly tested prior to recruitment. Procedures to protect the confidentiality and integrity of the databases and documents will be reviewed by the biostatistician prior to patient recruitment and periodically during the study. To maintain the confidentiality of patient information, all patients will be identified by study numbers. The password security system will be used to assign appropriate levels of computer privileges to different database users to ensure that all personnel remain blinded. Computer files with patient names will be password-protected, with access restricted to staff who use this information to recruit patients, obtain follow-up data, and interact with patients who report adverse events.

During the intervention phase of the trial, we will continuously monitor the nurses' interventions and provide focused supplemental training as needed. After auditing to ensure adherence to the protocol, initials from the charts will be removed and stored in locked filing cabinets that are only accessible to study personnel. All data analysis files will be password protected.

### Protection of human subjects and assessment of safety

Our study protocol was approved by the Primary Care Research Committee and Mallorca Ethical Committee of Clinical Research (IB 969/08 PI).

### Adverse Events

Participants will be asked about adverse events at each visit. We define an adverse event as any unfavorable or unintended sign, symptom, or disease that could reasonably be associated with the use of AHT. If a patient develops a serious adverse event (death, a life-threatening event, inpatient hospitalization or prolongation of existing hospitalization, persistent or significant disability/incapacity, cancer, or fetal exposure) during the course of the study, it will be reported to the Spanish Agency of Medication Registry for Drug Adverse Events.

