**Figure 1 F1:**
[figure not shown]
**Study design Flow-chart**.

Table 1 summarizes the measures and variables according to the timeline. Participants will be studied for 1 year following randomization. Primary and secondary outcomes will be assessed by an external nurse who will be blinded to treatment assignment after 12 months. The primary outcome will be systolic BP. Secondary outcomes will include diastolic BP, direct costs, and the number of patients who required treatment to yield one patient with normalized BP.

**Table 1 T1:** Measures, variables and timeline

VISIT	-1	0	1	2	3	4
Time (months)	-1	0	1	3	9	12
Blood pressure measurement inclusion criteria	X	X				
Morisky-Green and Haynes-Sackett tests	X					
Inclusion and exclusion criteria	X					
Comorbidities		X				
Blinded blood pressure measurement						X
Medication use						X
Adverse effects to medication		X				X
Medical consultation, cardiovascular events and hospital admission.						X
Checklist and time duration of intervention components (Intervention group)			X	X	X	
Motivational interview (Intervention group)			X	X	X	
Pill reminder (Intervention group)			X			
Family support (Intervention group)			X	X	X	
Blood pressure self-recording (Intervention group)			X	X	X	
Simplification of dosing regimens (Intervention group)			X			

Information bias will be minimized by use of a design that provides the maximum possible level of masking for studies of non-pharmacological intervention. In particular, the outcome assessor, data analyst, and physician will all be blinded to patient allocation. Misclassification, if any, is expected to be non-differential. Quality control will include recording of patient adherence to interventions, inclusion and follow-up monitoring, and quality supervision of data entry. We will perform an intention-to-treat analysis of the data; that is, the analysis will be by randomized assignment regardless of participation in intervention sessions.

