### Multifactorial Intervention

The intervention consists of five components that will be delivered during three interventional visits of about 30 min each. Use of a detailed intervention protocol and comprehensive motivational interview training is intended to increase the effectiveness of interventions. The study nurses will carefully document each component of the multifactorial intervention that they perform by use of specially designed intervention visitation documents and will register the time and the duration of each component of the intervention.

The five components of the intervention are:

1. ***Motivational interview: ***This will be based on the Health Belief Model [24] and the Prochaska and DiClemente stage of change [25], and will try to resolve ambivalences that patients have regarding medication and explore perceptions that patients have about their ability to control events (locus of control).

2. ***Pillbox Reminder: ***A pillbox organizer with seven compartments will be given to the patients. They will self-fill it with one pill for each day of the week. Use of the pillbox will be explained to patients in the intervention group.

3. ***Family Support: ***Patients will designate one person in their household who will be responsible for reminding and monitoring medication intake. The designated person must accept responsibility of reminding the patient to take medication and of supervising pill intake. If a patient lives alone or does not wish to involve a family member or carer, they do not need to designate anybody. Thus, this part of the intervention is not mandatory.

4. ***BP measurements and AHT reminder forms: ***Twelve forms (one per month) and a table will be completed by the patient and nurse and used to record the date and hour of all BP readings (including gaps). AHT dosage and a telephone contact number will also be recorded on each form. This information will be frequently updated. The forms will be provided to patients and nurses at visit 0, and patients will be asked to bring them to all subsequent visits.

5. ***Simplification of dosing regimens: ***AHT dosage will be recorded at visit 0, and pharmacists will simplify the dosing regimen when possible at subsequent visits.

Visit 1 (first month, 40 min total): motivational interviewing (25 min), pill reminder (5 min), self-recording of BP (5 min), family support, when possible (5 min).

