An analysis of direct costs and outcomes for patients in both groups will be conducted by a nurse blinded to patient allocation. Clinical record review and detailed self-reported data on costs of healthcare utilization, clinical tests, and medication will be considered. All resources utilized will be multiplied by the appropriate cost using nationally applicable cost data. The cost of resource utilization (primary care visits, hospital admissions, clinical testing) will be estimated using the healthcare costs published in the *National Official Journal of Spain *or *Regional Officials Journal*. Costs of all AHTs will be calculated using prices published in the catalogue of pharmaceutical compounds by the Spanish Board of Pharmacists. Intervention costs will also consider the time needed to train nurses and the time of each intervention visit.

The primary health outcome for the cost analyses is BP reduction, which will be calculated using direct costs. The measure of "relative value for money" from the intervention is the incremental cost-effectiveness ratio calculated from the additional cost for a benefit of 1 mmHg reduction.

Analysis of costs may require variable transformation, but can be modeled using multivariate linear regression without a baseline value for costs because this value will be unknown. We will adjust for age, sex, and comorbidities that may affect cost. We recognize that we will have low statistical power to detect even moderate cost differences between the two groups.

Each nurse will provide intervention to a group of patients, so we will also measure the effect of individual nurses on outcome by multilevel analysis to determine if there is a significant variation across nurses that cannot be explained by random variation, also we will establish a number maximum of 10 patients per nurse to minimize this effect.

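### The adverse-event definition is tied to antihypertensive drug use, although a behavioural package is what is randomised, and it is unclear whether that condition also limits the serious events

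*Protocol article*

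**What the plan says.** The Adverse Events section of the protocol article defines an adverse event as "any unfavorable or unintended sign, symptom, or disease that could reasonably be associated with the use of AHT". On timing it says: "Participants will be asked about adverse events at each visit". Table 1 has a row of matching scope, "Adverse effects to medication", marked at visits 0 and 4 (baseline and month 12).

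The same section then turns to serious events: "If a patient develops a serious adverse event (death, a life-threatening event, inpatient hospitalization or prolongation of existing hospitalization", followed by lasting disability, cancer and fetal exposure. If one occurs during the study, "it will be reported to the Spanish Agency of Medication Registry for Drug Adverse Events".

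Table 1 has a separate row, "Medical consultation, cardiovascular events and hospital admission", marked at month 12. It carries no condition on cause and, unlike the rows for the intervention components, is not limited to the intervention group. The Statistical Analysis section also uses admissions for costing: "The cost of resource utilization (primary care visits, hospital admissions, clinical testing) will be estimated".

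The Multifactorial Intervention section describes five components: interviewing, a weekly pill organiser, a household helper, home blood pressure logging and a simpler regimen where possible. Of the helper it says: "The designated person must accept responsibility of reminding the patient to take medication and of supervising pill intake".

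**The concern.** The definition puts a causality judgement inside the term adverse event, and the cause it names is the background drug treatment, which both arms receive. The arms differ by the package. A safety definition should be able to register harm from what is randomised, whichever way that harm arises. This one registers it only when it passes through the drugs.

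It also leaves out, on a literal reading, the events that come from not taking the drugs. The Background names these as the risk of this population: it links low adherence to cardiovascular morbidity and more hospital use.

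The serious-event sentence adds a second difficulty. A serious adverse event is, by its name, an adverse event first, yet the list is worded by seriousness alone and includes events with no evident tie to AHT. Two sites could count the same admission differently and both claim to follow the text. At stake are the completeness and consistency of the safety count.

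**Working it through.** No figure in the document bears on this point, so nothing can be recalculated. The check is to take the stated rules and ask where different kinds of event would be recorded. The examples are illustrations; the article does not report or predict any of them.

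| Event | Adverse-event definition | Serious list | Table 1, month-12 row on consultations, cardiovascular events and admissions |
|---|---|---|---|
| Drug reaction, or dosing error from a misfilled pill organiser | Inside: acts through AHT | If serious | If it led to a consultation or admission |
| Distress from an interview or from household supervision, no care sought | Outside | No | No |
| Stroke with admission in a patient not taking AHT | Outside unless attributed to AHT | Depends on the reading | Yes, either arm |
| Cancer diagnosis | Outside unless attributed to AHT | Depends on the reading | Only through a consultation or admission |

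1. **Row 1.** The most direct route of harm for an adherence package, greater or mistaken exposure to the drugs, is covered.

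2. **Row 2.** A harm of the package that does not act through AHT and leads to no consultation or admission has no stated place anywhere in the article.

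3. **Row 3.** An event of uncontrolled blood pressure is recorded, but as clinical-event or resource-use data. It enters the adverse-event count only if someone judges it related to AHT.

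4. **The serious list, read as restricted.** If a serious adverse event must first satisfy the definition, the drug registry is a coherent destination. The stroke in row 3 and the cancer in row 4 are then not serious adverse events unless attributed to AHT.

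5. **The serious list, read as unrestricted.** If the list stands on its own wording, both events are serious adverse events. The list then goes beyond the definition one sentence before it, and events unrelated to any drug are sent to a registry for drug reactions.

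6. **Result.** Neither reading makes the definition, the list and the registry fit together with full coverage of the events, and the text does not choose between them.

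A neighbouring mismatch should be settled in the same edit. The Adverse Events section has participants asked at every visit, whereas Table 1 marks adverse effects only at visits 0 and 4. The Control group section gives controls contact only at baseline and month 12.

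**The case against.** The best defence is that the plan runs two consistent streams. One is for drug reactions: the AHT-tied definition, the matching Table 1 row and the drug registry. The other is for clinical events: consultations, cardiovascular events and admissions, collected at month 12 in both arms whatever the cause and supported by record review for costing. On this view the complaint is largely about labels. The serious-event sentence, read plainly, has no AHT qualifier and may cover all such events. Details of the event form may also sit in a fuller protocol.

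Much of this stands, and it rules out several stronger readings that a reader might infer:

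- **That a causality filter keeps events from being recorded.** Table 1 contradicts this for cardiovascular events and admissions. They may be missing from the adverse-event count, but not from the trial's data.
- **That the safety comparison leans against the intervention.** One could argue that drug reactions rise with adherence while events of non-adherence are left out. The article plans no between-arm test of adverse events and gives no event rates, so the direction is conjecture.
- **That a particular number of events would be omitted.** Any count would need rates that the article does not give, and for serious events it would also assume the restricted reading.
- **That nurses who know the arm decide attribution.** The article does not say who decides. Table 1 places adverse effects at baseline and month 12, and a blinded external nurse assesses the month-12 outcomes.

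The defence does not dispose of two things. Package harms outside the drug route have no stated place unless they lead to a consultation or admission, and the scope of the serious list is open. Both arise from rules the article states, so they are not details left to another document.

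**Conclusion.** The point holds in a limited form. The stated definition is one of adverse drug effects, applied to a trial of a behavioural package. It leaves out package harms that do not act through AHT, and it leaves out events of uncontrolled blood pressure unless they are attributed to AHT. Whether the same condition limits the serious events is ambiguous; the text does not show that it does.

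The effect is confined to what is counted and reported as safety data. It cannot be sized from the document. The primary systolic blood pressure analysis is unaffected, and cardiovascular events and admissions remain available from the month-12 collection. The conclusion rests on taking the definition literally and on reading the unlabelled Table 1 row as applying to both arms. This is a worthwhile, inexpensive improvement and not a threat to the trial's main result.

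**What to change.** In the Adverse Events section:

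- Define an adverse event as any untoward medical occurrence after randomisation, in either arm and regardless of cause.
- Record relatedness to AHT and relatedness to the intervention as two separate fields, so that attribution no longer decides whether an event counts.
- State that the serious-event list applies regardless of cause, and link it to the cardiovascular events and admissions already collected under Table 1.
- Reconcile the drug-registry sentence with that definition, so that it is clear which events it concerns.
- Align the wording on when participants are asked with the Table 1 schedule.

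The cost is the rewording of one section, a matching edit to Table 1 and two fields on the event form. The downside is somewhat more events to record, most of them unrelated to either the drugs or the package. The main clinical events are already being collected, so the added burden should be modest.

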### Statistical Analysis

The primary statistical analysis will determine if our multifactorial intervention to improve AHT adherence is effective in lowering systolic BP and if the intervention is cost-effective. We will use intention-to-treat analysis for all data analyses; that is, all randomized patients will be included in the analysis, regardless of participation in any treatment sessions. This approach reduces the bias that may occur when participants who do not receive assigned treatments are excluded from analysis. All tests will be two-sided and α-values of 0.05 will be considered statistically significant.

We will test for significant differences between baseline characteristics of control and intervention groups. We will perform descriptive analysis, with continuous variables summarized by their means and standard deviations for normal distributions, and by median and 25^th ^and 75th percentiles for non-normal distributions.

In bivariate analysis, we will compare systolic and diastolic BP between the intervention and control groups at visit 4 (12th month) using the Student's *t*-test if both sample groups had normal distributions or the Mann-Whitney U test against the usual null hypothesis of no difference between means if the sample groups had non-normal distributions. We will also calculate 95% confidence intervals to assess the clinical significance of our treatment.

In multivariate analysis, we will adjust for clinical inertia (physicians blinding and number of medication changes) in a multiple linear regression model.

We will test for a significant difference in the percentage of patients with controlled BP (according to ESH/ESC guidelines) in the intervention and control groups using the χ^2 ^test. We will estimate relative and absolute risk reduction and the number needed to treat, defined as the estimated number of patients who need to be treated with the intervention (rather than the usual care) for one additional patient to be controlled. The 95% confidence intervals for these calculations will be provided. The number needed to treat is calculated as the reciprocal of the difference between the proportion of patients controlled in the intervention group and the control group.

An analysis of direct costs and outcomes for patients in both groups will be conducted by a nurse blinded to patient allocation. Clinical record review and detailed self-reported data on costs of healthcare utilization, clinical tests, and medication will be considered. All resources utilized will be multiplied by the appropriate cost using nationally applicable cost data. The cost of resource utilization (primary care visits, hospital admissions, clinical testing) will be estimated using the healthcare costs published in the *National Official Journal of Spain *or *Regional Officials Journal*. Costs of all AHTs will be calculated using prices published in the catalogue of pharmaceutical compounds by the Spanish Board of Pharmacists. Intervention costs will also consider the time needed to train nurses and the time of each intervention visit.

The primary health outcome for the cost analyses is BP reduction, which will be calculated using direct costs. The measure of "relative value for money" from the intervention is the incremental cost-effectiveness ratio calculated from the additional cost for a benefit of 1 mmHg reduction.

Analysis of costs may require variable transformation, but can be modeled using multivariate linear regression without a baseline value for costs because this value will be unknown. We will adjust for age, sex, and comorbidities that may affect cost. We recognize that we will have low statistical power to detect even moderate cost differences between the two groups.

Each nurse will provide intervention to a group of patients, so we will also measure the effect of individual nurses on outcome by multilevel analysis to determine if there is a significant variation across nurses that cannot be explained by random variation, also we will establish a number maximum of 10 patients per nurse to minimize this effect.

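### The claim that all randomised patients are analysed does not fit the stated month-12 test, which cannot use the roughly 20% expected to have no month-12 value unless values are supplied

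*Protocol article*

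**What the plan says.** Four parts of the protocol article bear on who is analysed.

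- **Statistical Analysis, the claim.** Intention-to-treat is to govern all analyses, meaning that "all randomized patients will be included in the analysis, regardless of participation in any treatment sessions".
- **Statistical Analysis, the method.** For the BP outcomes, "we will compare systolic and diastolic BP between the intervention and control groups at visit 4 (12th month"), by Student's t-test or, if the distributions are not normal, by the Mann-Whitney test. The multiple regression described next adjusts for physician blinding and the number of medication changes, not for baseline BP.
- **Sample size section.** The calculation is made "Assuming a standard deviation of 15 mmHg and a 20% loss to follow-up", and after a contamination factor the target is 320 patients.
- **Data collection and management.** Among the counts to be reported for patient flow is "the number of patients who complete the trial and are included in the analysis".

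Table 1 places the blinded BP measurement at visit 4 (month 12) only. BP is also measured for eligibility at visits -1 and 0. The Control group section has controls contacted at baseline and at month 12.

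**The concern.** The Statistical Analysis section makes a statement about who is counted: everyone randomised. The test it names needs a month-12 BP from each patient. The plan itself expects a fifth of patients to be lost. The allowance for loss in the sample size, and the flow count that joins completing the trial to being analysed, both suggest a comparison of completers.

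Two things are at stake. First, the report could claim a property that the analysis does not have. Second, an unadjusted comparison of observed patients takes no account of whether those lost started with higher or lower BP. There is some reason to ask. Patients are recruited for low adherence, which the Background section links to raised BP, and scheduled contact differs between arms: three intervention visits against none for controls between baseline and month 12.

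**Working it through.** **Inputs.** 320 patients, 1:1 allocation, 20% loss, target difference 6 mmHg, standard deviation 15 mmHg, two-sided 0.05, all from the protocol article. Loss by arm and the BP of lost patients are not given, so any value for them is an assumption.

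**1. The plan's own figures.** The section aims for "adequate statistical power to detect a clinically significant difference of at least 6 mmHg at 1 year" without a percentage, so the 110 per group cannot be settled. With n = 2(z₀.₉₇₅ + z_power)²(15/6)², divided by 0.80 for loss:

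| Power | n per arm | After 20% loss |
|---|---|---|
| 75% | 87 | 109 |
| 80% | 99 | 124 |
| 90% | 132 | 165 |

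The stated 110 fits about 75% power, and 2 × 110 × 1.41 = 310.2 against the stated 320. That is a separate matter. The check below takes 320 and 20% as given.

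**2. Patients without the primary outcome.** 0.20 × 320 = 64, leaving 256, or 128 per arm if loss is equal.

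**3. Is this a power problem?** With 128 per arm the standard error is 15 × √(2/128) = 1.875 mmHg. For 6 mmHg, 6/1.875 − 1.96 = 1.24, which is 89% power. If 15% contamination dilutes the effect to 0.85 × 6 = 5.1 mmHg, 5.1/1.875 − 1.96 = 0.76, which is 78%. Loss has been allowed for in the numbers. The point here is the analysed population, not sample size.

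**4. Can the stated test include the 64?** Both candidate tests need a visit-4 value. Table 1 schedules no earlier post-randomisation blinded BP, and self-recorded BP is an intervention-group item. No interim measurement is therefore planned in both arms that could stand in. The 64 enter only if values are supplied, and the article names no such step.

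**5. What can be said about bias?** Let p be the share missing and d the mean BP of missing minus observed patients in each arm (I intervention, C control). The full-arm mean is the observed mean plus p × d, so a comparison of observed patients overstates the BP reduction by

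p_I × d_I − p_C × d_C.

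With assumed values:

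| Loss I / C | d_I / d_C (mmHg) | Overstatement (mmHg) |
|---|---|---|
| 20% / 20% | 5 / 5 | 0 |
| 20% / 20% | 5 / 0 | 1.0 |
| 20% / 20% | 10 / 0 | 2.0 |
| 15% / 25% | 5 / 5 | −0.5 |
| 25% / 15% | 5 / 5 | +0.5 |

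The result is zero, positive or negative according to the assumptions. It is zero whenever p_I × d_I = p_C × d_C, even if drop-out depends strongly on BP.

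**6. What baseline adjustment adds.** If loss depends on baseline BP, the patients observed in the two arms may differ at baseline, and the unadjusted test leaves that difference in the estimate. A regression on baseline systolic BP takes it out, provided the model is right and loss does not otherwise depend on the outcome.

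**The case against.** The strongest reply is that this is a wording point. The intention-to-treat sentence speaks of session attendance, and its stated reason is to avoid excluding patients who did not receive their assigned treatment. The Overview section defines the principle as analysis by assignment. The stated method delivers that. A t-test can also be run on imputed data, and handling of missing outcomes is commonly left to a full protocol or analysis plan, neither of which is shown. The flow count is an item for a CONSORT report, defines no analysis set, and stands beside a separate count of patients who give follow-up data. Enlarging a sample for loss is routine.

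Most of this stands, and it rules out three stronger readings that a reader might infer.

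- *That the plan abandons intention-to-treat.* It does not: patients are compared in their assigned arm whatever their attendance.
- *That the plan excludes the lost 20%.* No complete-case rule is stated. That reading is an inference from the test, the sample-size allowance and the flow count.
- *That drop-out bias is uncontrolled, or that the comparison is unbiased only if drop-out is unrelated to BP.* Neither follows, as step 5 shows. Differential loss is not settled either: controls may visit the study nurses and are contacted at month 12 for the same outcomes.

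What the reply does not remove is the mismatch itself. The claim about all randomised patients is published, and so are the test and the loss rate. The three do not fit together as written. This does not depend on which imputation method an unseen document might contain.

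**Conclusion.** The concern holds in a limited form. The claim that every randomised patient is analysed is not met by the stated month-12 comparison. At the plan's own loss rate about 64 of 320 patients would not contribute unless values are supplied, and the flow wording also points towards an analysis of completers. In addition, the unadjusted test does nothing about drop-out related to baseline BP, although baseline BP is collected.

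Only the 64 and the 256 follow from the document, and they assume that the 20% loss occurs. The mmHg figures in the working are illustrations on assumed values. Neither the size nor the direction of any bias can be derived from the article. The matter should be corrected, and it does not by itself undermine the design.

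**What to change.** 1. **Population.** Restate the primary population as all randomised patients with a month-12 BP, analysed as randomised. Make the sample-size section, the patient-flow wording and the Statistical Analysis section agree with it.
2. **Primary analysis.** Replace the unadjusted test with a regression of month-12 systolic BP on arm and baseline systolic BP, with nurse as a random effect. Baseline BP is already collected, nurse is the stratification factor, and the plan already intends a multilevel look at nurses.
3. **Sensitivity analysis covering all 320.** Impute month-12 values multiply, by arm, from baseline BP, age, sex and comorbidities, and repeat with a shift applied to the imputed values. Do not use nurse as a fixed imputation factor. At most 10 patients per nurse means at least 320/10 = 32 nurses, so at most about 5 patients per arm for each nurse, and 4 after 20% loss, which is too few.

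The cost is revised wording and a little more analysis, with no new data. The interval in the sensitivity analysis may be wider.
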